##### Patient expectations and satisfaction with outcomes

2.5.2.4

Patient expectation and satisfaction with the curative effect will be investigated using the expectation and treatment credibility scale (ETCS).^[29]^ The ETCS includes 4 statements with a yes/no response: ETCS1: I am sure this treatment will relieve my pain; ETCS2: I think this treatment is reasonable; ETCS3: I will recommend this therapy to my friends; ETCS4: I believe this therapy can cure other diseases. Both groups will complete the ETCS questionnaire 3 minutes before treatment and 3 minutes after the 30-minute treatment.

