**Methods::**

The study will be a randomized controlled trial conducted from May 1, 2019 to May 30, 2020 that includes 78 students from Shanghai University of Traditional Chinese Medicine who have primary dysmenorrhea and meet the eligibility criteria. Participants will be randomly divided into 2 groups in a 1:1 allocation ratio. The intervention group will use the acupressure wrist-ankle strap equipped with tip compression component parts on the internal side; the control group will use the nonacupressure wrist-ankle strap with the tip compression parts removed. All participants will be treated for 30 minutes on the 1st day of menstruation. The primary outcome is the pain intensity score measured by the visual analog scale. The secondary outcomes are the onset time of analgesia, the pain threshold at Yinlingquan (SP 9), skin temperature at Guanyuan (CV 4), and expectations and satisfaction of patients as investigated via the expectation and treatment credibility scale.

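### Satisfaction is a named secondary outcome, but the only scale assigned to it has no direct satisfaction item, so expectation or credibility answers could be reported as satisfaction

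*Protocol article*

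**What the plan says.** The Abstract (Methods) ends its list of secondary outcomes with "expectations and satisfaction of patients as investigated via the expectation and treatment credibility scale". Section 2.5.2.4 carries both expectation and satisfaction in its heading and ties the satisfaction part to the treatment effect: "Patient expectation and satisfaction with the curative effect will be investigated using the expectation and treatment credibility scale (ETCS").

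The same section describes the instrument: "The ETCS includes 4 statements with a yes/no response". It then lists all four:

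- The first is about expected relief: "ETCS1: I am sure this treatment will relieve my pain"
- The second is about whether the treatment makes sense to the participant: "ETCS2: I think this treatment is reasonable"
- The third is about passing it on to others: "ETCS3: I will recommend this therapy to my friends"
- The fourth is about its use beyond period pain: "ETCS4: I believe this therapy can cure other diseases"

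On timing it says: "Both groups will complete the ETCS questionnaire 3 minutes before treatment and 3 minutes after the 30-minute treatment". Section 2.9 repeats that the scale is completed before and after treatment.

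**The concern.** The outcome that is named and the content of the scale assigned to it do not match. Being satisfied with an effect is a judgement on something already experienced. The scale, as its name says, covers expectation and credibility, and its statements are the same before and after the strap is worn.

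Two things are at stake. First, a shift in the answers on reasonableness or on other diseases could be presented as satisfaction with pain relief. A woman with no relief can answer yes to both, and a woman with good relief can answer no to the last. The Introduction describes the strap as a device that patients operate themselves, so readers would make use of a statement about satisfaction. Second, section 2.10 plans to relate expectations to the effect. If the same four answers serve both as expectation and as satisfaction, a possible predictor and an outcome are mixed.

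**Working it through.** The point rests on wording, so the check is to set the items, the timing and the other forms beside the named outcome.

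**Step 1: item content against the named outcome (section 2.5.2.4).**

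| Item | What it asks | Direct question on satisfaction with the effect? |
|---|---|---|
| ETCS1 | Expectation of relief | No |
| ETCS2 | Credibility | No |
| ETCS3 | Willingness to recommend | No; after treatment, an indirect proxy |
| ETCS4 | Belief about other diseases | No |

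Direct items: 0 of 4. Possible proxy: 1 of 4.

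**Step 2: does the timing turn an item into a satisfaction measure?** Before treatment there is no effect to be satisfied with, so only the post-treatment form could serve. On that form ETCS1, ETCS2 and ETCS4 remain statements of expectation, credibility and general belief. Only ETCS3 plausibly takes in the experience of the session, and even that link is loose. A woman without relief may still recommend a portable, non-invasive strap, and a woman with relief may not recommend it for reasons unrelated to pain.

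**Step 3: does another form fill the gap?** Sections 2.6 and 2.9 name a general information form, the Cox menstrual symptom scale and the syndrome differentiation form. All are completed at baseline or before treatment, so none can record satisfaction with the effect.

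**Step 4: does the analysis text say which response stands for satisfaction?** Section 2.10 names one analysis in this area, a general linear model relating expectations to the effect. It does not mention satisfaction. This silence is not counted as a fault, because an analysis plan may supply the detail. It only shows that the article does not resolve the mismatch.

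**Step 5: does any figure change?** The protocol gives no figure for this outcome. Its one calculation (section 2.7) uses VAS inputs only: σ = 1.4, D1 = 1, M = 4, ρ = 0.7, two-sided α = 0.05, β = 0.1. With equal correlation between measurements, the SD of the mean of four is 1.4 × √((1 + 3 × 0.7)/4) = 1.2325. The size per group is 2 × (1.2325 × (1.960 + 1.282)/1)² = 31.92, rounded up to 32, which matches the stated 32. Satisfaction does not enter this calculation.

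**The case against.** A reader might infer that satisfaction is not measured in either arm, or that this secondary outcome cannot be concluded on at all. The text does not support either statement. Both groups answer the recommendation item after wearing the strap, and that is a plausible though weak indicator of satisfaction. The named outcome is a pair, and its expectation half is measured.

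A reader might also infer that the trial is bound to misreport. That is not established: section 2.10 plans no satisfaction score and no comparison of satisfaction between groups. Misreporting is a risk that the wording leaves open.

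Further objections, and what stands of each:

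- *Which response represents satisfaction can be left to the analysis plan.* That is true of a scoring rule. But an analysis plan cannot supply an item that was never asked; it could only choose among four statements, none of which is direct.
- *The statement on relief is in the future tense even after treatment, but only the English wording is visible.* The participants are students at a Shanghai university, and the form may be in another language (an assumption). The objection is fair, so the point does not rely on tense.
- *The assessment schedule (Figure 5) is not shown and might list a separate satisfaction item.* This cannot be excluded. It is unlikely, since the Abstract and section 2.5.2.4 both assign satisfaction to this scale.
- *The consequence is small.* This stands. Relief itself is captured by the VAS (section 2.5.1) and by participant-reported onset time (section 2.5.2.1).

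**Conclusion.** The point holds in this form: satisfaction with the effect is named as part of a secondary outcome, the text assigns it to one scale only, and that scale has no direct item for it (0 of 4). Willingness to recommend, answered after treatment, is at best an indirect proxy (1 of 4) and is not declared as such. Followed as written, answers on expectation or credibility could be reported as satisfaction.

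The size is modest. One half of one secondary outcome is affected; the primary outcome, the sample size and the expectation half are not. The conclusion assumes that the four statements listed in section 2.5.2.4 are the whole scale as administered and that Figure 5 adds no separate satisfaction item.

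**What to change.** Add one item to the post-treatment form only, in both groups, asking how satisfied the participant is with the pain relief just obtained. The 100-mm line already used for pain would serve. Compare the groups on that item, and analyse the four existing statements only as expectation and credibility.

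The cost is one question, with no extra visit and no more participants. It does need a protocol change. Section 3.1 reports that recruitment began on May 1, 2019, so women treated before the change would have missing values on the item, and the report should state how many.

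If no item is added, rename the outcome as expectation and credibility in the Abstract and in section 2.5.2.4, and draw no conclusion on satisfaction. At most, report the post-treatment answer to ETCS3 as an indirect proxy, declared as such before the data are analysed. Either route is a change of wording only.

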### Study procedure

2.6

Baseline demographic and clinical characteristics will be recorded before study commencement. Participants will complete a general information form, the Cox menstrual symptom scale (CMSS),^[30]^ the traditional Chinese medicine (TCM) syndrome differentiation form,^[31]^ and provide written informed consent. Subjects who meet the eligibility criteria will be enrolled, grouped, and given corresponding interventions. The schedule of enrolments, allocation and assessments is given in Figure 5. The participant flow diagram is illustrated in Figure 6.

**Figure 5 F5:**
[figure not shown]
The schedule of enrolments, allocation, and assessments.

**Figure 6 F6:**
[figure not shown]
Flow diagram of the proposed study.

### Sample size calculation

2.7

The participants will be randomly divided into the acupressure wrist-ankle strap group (intervention group) and the nonacupressure wrist-ankle strap group (control group) in a 1:1 allocation ratio. Sample size calculation is based on the primary outcome, which is proposed to be the VAS. PASS 11 software (NCSS, Kaysville, UT) was used to calculate the required sample size. Based on the preliminary experiments, the mean baseline VAS was 74 mm with a standard deviation (*σ*) of 14 mm. The researchers expect the mean difference in the VAS score between the 2 groups (*D*1) will be 10 mm and the correlation between measurement points (*ρ*) will be 0.7, which is not moderately clinically meaningful but represents a minimally important difference. With the test levels set at *α* = 0.05 (2-sided), *β* = 0.1, *D*1 = 1, *M* = 4, *σ* = 1.4, *ρ* = 0.7, and the module selected as “Tests for Two Means in a Repeated Measures Design,” where *α* represents the probability of rejecting a true null hypothesis, *β* is the probability of obtaining a false negative with the statistical test, and *M* is the number of repeated measurements. Finally, at least 32 participants are required per group. Considering a 20% dropout rate, 39 participants will be enrolled in each group, giving a total of 78 participants.

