#### Primary outcome measures

2.5.1

The primary outcome measure is the abdominal pain intensity score assessed by VAS. Abdominal pain will be quantified using the VAS score as determined on a 100-mm horizontal line (0, no pain; 100, pain intolerable). On the VAS scale, the score is based on the horizontal distance from the leftmost pain free to the edge marked by the patient. The distance represents pain intensity. The VAS will be assessed at baseline (3 minutes before intervention) and at 5, 10, and 30 minutes (after the removal of the wrist-ankle strap).

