The purpose of this proposed RCT is to evaluate the immediate effect of the acupressure wrist-ankle strap in relieving pain caused by primary dysmenorrhea. The immediate analgesic effect of this acupressure wrist-ankle strap will be determined based on VAS scores, and the onset time of dysmenorrheic pain relief. The possible mechanisms of the acupressure wrist-ankle strap will be investigated by recording and observing the change in the pain threshold at Yinlingquan (SP 9), and the temperature change in the Guanyuan (CV 4) area. The CMSS and TCM syndrome scale will be used to analyze the correlation between the analgesic effect of the acupressure wrist-ankle strap and the TCM syndrome and severity of the disease.

The acupressure wrist-ankle strap is a physical therapy method that is portable, nontoxic, and easy to operate. Furthermore, the acupressure wrist-ankle strap is environmentally friendly due to its low-carbon characteristics and can be recycled.

If the proposed RCT can verify our hypothesis that the acupressure wrist-ankle strap is effective, it can be used as an immediate and effective physical intervention to relieve abdominal pain for patients with primary dysmenorrhea. The proposed RTC may also provide evidence for the analgesic effects of WAA and promote the application of WAA in clinical practice.

There exist some limitations of this proposed study. First, we will observe only the effects of one 30-minute treatment session, mainly focusing on the effect of 3 time points during the intervention period, for the main purpose of this study is to evaluate the immediate analgesic effect. Further work will be required to determine the longer-term effect of this device and whether this will be safe and acceptable for patients to use it frequently over several days. Second, the recruitment of participants is restricted to the students of a university with a great proportion of females, to include enough samples in a specific time period and to ensure good compliance of the participants. This will limit the external validity of the results. We will test the effects of this device with more diverse samples in the future study.

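### The sample size counts the pre-treatment VAS among its M = 4 measurements, so the test it sizes has about 68% power at 32 per group, not 90%

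*Protocol article*

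**What the plan says.** Section 2.7 (Sample size calculation) uses the PASS module "Tests for Two Means in a Repeated Measures Design" with "α* = 0.05 (2-sided), *β* = 0.1" and "D*1 = 1, *M* = 4, *σ* = 1.4, *ρ* = 0.7". The inputs are in centimetres. In millimetres, the text expects that "the mean difference in the VAS score between the 2 groups (*D*1) will be 10 mm", and reports from preliminary experiments that "the mean baseline VAS was 74 mm with a standard deviation (*σ*) of 14 mm". It explains that "M* is the number of repeated measurements". The result is 32 per group, raised to 39 per group (78 in total) for dropout.

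Section 2.5.1 (Primary outcome measures) gives the schedule: "The VAS will be assessed at baseline (3 minutes before intervention) and at 5, 10, and 30 minutes". The Discussion describes the study as "mainly focusing on the effect of 3 time points during the intervention period".

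Section 2.10 (Statistical analysis) plans a repeated measures ANOVA by group and observed time, with a mixed model if needed. Covariance adjustment is foreseen only if baseline characteristics turn out imbalanced.

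**The concern.** This type of calculation sizes the group difference averaged over the M measurements, and it takes the full difference D1 to be present in that average. The schedule contains one score that treatment cannot affect and three that it can. With M = 4 the pre-treatment score is in the average, where it adds nothing to the expected difference and pulls the mean effect down.

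The planned analysis can repeat the fault. If baseline is one of the observed times in the repeated measures ANOVA and the group main effect is read as the answer, that effect is diluted in the same way. A real 10 mm benefit, which section 2.7 calls a minimally important difference, would then be missed about one time in three, although the plan promises one in ten.

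A related weakness is that the 14 mm SD describes baseline pain in the pilot work and is carried unchanged to scores after treatment, where the spread may differ.

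**Working it through.** **Inputs.** From section 2.7: two-sided α = 0.05, β = 0.1, D = 10 mm, σ = 14 mm, ρ = 0.7, M = 4. From section 2.5.1: one score before treatment and three after it starts.

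**Formula.** For a time-averaged difference with equal correlation ρ between all measurements, the variance of a participant's mean score is σ²·f(M), with f(M) = [1 + (M − 1)ρ]/M. Per group,

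n = 2(z₀.₉₇₅ + z₀.₉₀)²·σ²·f(M)/D², where (1.960 + 1.2816)² = 10.507.

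**Step 1: reproduce the plan's figure.**
- M = 4: f = (1 + 2.1)/4 = 0.775; n = 2 × 10.507 × 196 × 0.775/100 = 31.92, so 32. This is the stated figure.
- M = 3: f = (1 + 1.4)/3 = 0.80; n = 32.95, so 33.
- M = 1: f = 1; n = 41.19, so 42.

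Of these, only M = 4 returns 32.

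**Step 2: put in the effect the design can produce.** With true differences of 0, 10, 10 and 10 mm at baseline, 5, 10 and 30 minutes, the four-score average is 30/4 = 7.5 mm.
- SE at 32 per group: 14 × √0.775 × √(2/32) = 3.08 mm. Power = Φ(7.5/3.08 − 1.96) = 68.2%. The t-based figure is 66.9%, and simulation of 20,000 trials gives 67.0%.
- SE at 39 per group: 14 × √0.775 × √(2/39) = 2.79 mm. Power = 76.6% (75.6% by t).
- For 90%: n = 2 × 10.507 × 196 × 0.775/56.25 = 56.75, so 57 per group.

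**Step 3: an effect that builds up.** As an assumption, since the article gives no time profile, take 0, 5, 7.5 and 10 mm. The average is 22.5/4 = 5.625 mm, and main-effect power at 32 per group is Φ(5.625/3.08 − 1.96), about 45%.

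**Step 4: other analyses with the same σ and ρ, 10 mm at each post-baseline time.** The covariate-adjusted variance factor is f(3) − ρ² = 0.80 − 0.49 = 0.31 for the mean of three scores, and 1 − 0.49 = 0.51 for the 30-minute score.

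| Analysis | n per group for 90% | Power at 32 | Power at 39 |
|---|---|---|---|
| Four-score mean, baseline included | 57 | 68% | 77% |
| Mean of three post-baseline scores | 33 | 89% | 94% |
| Mean of three, baseline as covariate | 13 | 99.9% | >99.9% |
| 30-minute score alone | 42 | 82% | 88% |
| 30-minute score, baseline as covariate | 22 | 98% | 99.3% |
| Group-by-time interaction, four times, 3 df | not derived | 97.5% | 99% |

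**Step 5: a larger post-treatment SD.** With an assumed SD of 20 mm and ρ still 0.7, power at 32 per group for the mean of three scores is 61% unadjusted and 95% with baseline as covariate.

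**The case against.** The strongest reply is that the trial itself is not underpowered. Section 2.10 does not say that the group main effect is the decisive test. With baseline among the repeated scores, the treatment effect also appears in the group-by-time interaction, which has 97.5% power at 32 per group for a constant 10 mm effect, and 91% (96% at 39) for the build-up profile in step 3. Dropping baseline from the calculation changes the requirement by one participant per group, and 39 will be enrolled. A single 30-minute session with intention-to-treat analysis may also leave nearly all 39 per group in the analysis, where the diluted test has about 77% rather than 68%.

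All of that stands. It shows that the sample is large enough for a well-chosen analysis. It does not make the stated 90% correct for the test that was sized, and the article does not name the interaction as primary.

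A second reply is that 10 mm might already be the average over all four scores. The difference after baseline would then have to be 10 × 4/3 = 13.3 mm. Section 2.7 says nothing of the kind, so this carries little weight.

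A third is that planning with a baseline SD is common and that an article may leave covariate details to the full protocol or SAP. That is fair: the SD calls for a sensitivity check and is not an error in itself. The mismatch between M = 4 and the schedule, however, lies within the article.

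**Conclusion.** The concern holds. The 32 per group comes from M = 4, and M = 4 fits the VAS schedule only if the pre-treatment score is counted. For the four-score group comparison that section 2.7 sized, power is about 68% at 32 per group and 77% at 39, against the planned 90%.

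These figures assume 10 mm at each of the three later times, no expected difference at baseline, SD 14 mm and a common correlation of 0.7. They apply to that test only. Other analyses compatible with section 2.10 have more than 90% power, so the attained power ranges from about 68% to above 97% at 32 per group, depending on which effect is read. That choice should be fixed before the data are seen. Because it concerns the stated power for the primary outcome, the point must be corrected, although the sample size need not change.

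**What to change.** In section 2.7, restate the calculation with M = 3 post-baseline measurements.

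In section 2.10, take baseline VAS out of the outcome vector and make it a prespecified covariate, in place of adjustment only when imbalance is found. Name one primary contrast: the baseline-adjusted group difference, either averaged over 5, 10 and 30 minutes or at 30 minutes.

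Report the power that 39 per group gives for that contrast, which exceeds 99% for either choice under the plan's own SD and ρ. It is also above 97% for either if only 32 per group are analysed. Add a short sensitivity table for a larger post-treatment SD.

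The cost is rewording two sections. Enrolment, visits and measurements stay as they are.

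### Enrolling 39 per group leaves 31.2, not the required 32, at the stated 20% dropout; the gap is small and one reworded sentence closes it

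*Protocol article*

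**What the plan says.** Section 2.7 (Sample size calculation) of the protocol article takes its standard deviation from preliminary experiments, where "the mean baseline VAS was 74 mm with a standard deviation (*σ*) of 14 mm". It then sets the target difference, "The researchers expect the mean difference in the VAS score between the 2 groups (*D*1) will be 10 mm", and assumes that "the correlation between measurement points (*ρ*) will be 0.7". The values entered in the software are on a centimetre scale: "With the test levels set at *α* = 0.05 (2-sided), *β* = 0.1, *D*1 = 1, *M* = 4, *σ* = 1.4, *ρ* = 0.7".

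The result is given as a floor: "Finally, at least 32 participants are required per group". The next sentence turns it into an enrolment target: "Considering a 20% dropout rate, 39 participants will be enrolled in each group, giving a total of 78 participants". No formula for the dropout adjustment is shown. The abstract repeats the total, saying that the trial "includes 78 students from Shanghai University of Traditional Chinese Medicine".

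Section 2.10 (Statistical analysis) plans both intention-to-treat and per-protocol analyses and fills missing values by carrying the last observation forward.

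**The concern.** A dropout allowance is meant to leave the required number once the assumed share has been lost. Here the required number, the assumed loss and the enrolment figure stand in two consecutive sentences, and the third does not follow from the first two. Anyone who takes 20% off 39 gets a number below the floor just stated.

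What is at stake is mainly the accuracy of a headline figure that readers can check for themselves, together with a slight loss of power if dropout really reaches 20%. The shortfall is one participant per group.

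**Working it through.** **Inputs (all from section 2.7).** Two-sided α = 0.05; β = 0.1, so power 0.90; difference 10 mm, entered as 1; standard deviation 14 mm, entered as 1.4; correlation ρ = 0.7; M = 4 measurements; 1:1 allocation; dropout 20%; 39 enrolled per group.

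**Step 1. Reproduce the stated 32.** For two means averaged over M equally correlated measurements,

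n per group = 2σ²(z₀.₉₇₅ + z₀.₉₀)² × [1 + (M − 1)ρ] / (M × D²)

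- 1 + 3 × 0.7 = 3.1, and 3.1/4 = 0.775
- 2 × 1.4² × (1.960 + 1.282)² / 1² = 41.19
- 41.19 × 0.775 = 31.92, rounded up to 32

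This matches the protocol, so the base calculation is not in question.

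**Step 2. Apply the stated dropout to the stated enrolment.**

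- 39 × (1 − 0.20) = 31.2 per group, below 32
- Over both groups: 78 × 0.8 = 62.4, against 2 × 32 = 64

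**Step 3. Enrolment that would keep 32.**

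- 32 / (1 − 0.20) = 40 per group, 80 in total

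**Step 4. Dropout that 39 does cover.**

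- (39 − 32)/39 = 7/39 = 17.9%
- In whole people, losing 7 leaves 32; losing 8 (8/39 = 20.5%) leaves 31

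**Step 5. How 39 may have arisen.**

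- 32 × 1.2 = 38.4, rounded up to 39, gives the stated figure
- 31.92/0.8 = 39.90, cut to 39, gives it too

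The protocol shows neither sum. Both routes end in the same shortfall.

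**Step 6. Effect on power.** The effective standard deviation is 1.4 × √0.775 = 1.2325. By the normal approximation, power = Φ(√(n/2) × 1/1.2325 − 1.960). The t column uses the noncentral t distribution with 2n − 2 degrees of freedom.

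| n per group providing data | Power, normal | Power, t |
|---|---|---|
| 31 | 89.1% | 88.2% |
| 31.2 | 89.3% | 88.4% |
| 32 | 90.1% | 89.2% |
| 39 (no loss) | 94.8% | 94.3% |

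The drop from 32 is 0.7 to 1.0 percentage points, depending on whether 31.2 or 31 is used.

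**The case against.** Several points can fairly be made for the plan as written.

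- **Intention-to-treat keeps the dropouts.** Section 2.10 carries last observations forward, so a participant who leaves after the baseline VAS stays in the intention-to-treat analysis, and the number analysed need not fall to 31. This stands, and it limits the point: the shortfall applies to the per-protocol set, or to dropouts without VAS data. It does not remove the point. Carried-forward values do not restore the information lost, and the protocol itself inflates for dropout, so its 32 is meant as the number left after losses.
- **The session is short.** Treatment is a single 30-minute session, and the Discussion expects good compliance, so actual loss may be well under 20%. That may be so, but the documents give no observed dropout rate. It questions the choice of 20%, not the sum that follows from it.
- **An allowance is a convention, not a guarantee.** If each participant drops out independently with probability 0.2, a given group keeps at least 32 with probability about 0.47 when 39 are enrolled and about 0.59 when 40 are. This also stands: the gain from two more participants is slight, which argues for correcting the text and leaving recruitment alone.

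Two stronger readings are tempting and go too far. A reader might infer that the authors certainly multiplied by 1.2. The match is exact, but no formula is given and another route also yields 39, so the most that can be said is that the figure is consistent with it. A reader might also infer that the trial becomes underpowered, or falls below its minimum in every analysis. The intention-to-treat plan does not support that, and the loss is at most about one point. By the t-based calculation, power at 32 is already 89.2% before any dropout, so a shortfall from exactly 90% should not be put down to the dropout step alone.

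**Conclusion.** The enrolment sentence is wrong as written, and the matter is minor. At 20% dropout, 39 per group leaves 31.2 on average, against a stated minimum of 32; keeping 32 would take 40 per group, 80 in total. The shortfall is one participant per group, and normal-approximation power is about 89% in place of 90.1%.

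The contradiction needs only the three stated figures. The power figures also assume the protocol's difference, standard deviation and correlation, equal correlation between all four measurements, and that dropouts contribute no data to the analysis concerned. Nothing here threatens the validity of the trial or shows that 78 participants are too few for its purpose.

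**What to change.** Keep 78 and replace the enrolment sentence in section 2.7 with wording such as:

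> 39 per group allows for up to 17.9% dropout; at 20% dropout about 31 per group would remain, giving about 89% power (normal approximation) under the stated inputs.

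The cost is one sentence. The total in the abstract stays as it is, and recruitment, which the Trial status section says began on May 1, 2019, is unaffected. Raising enrolment to 80 would also make the figures agree, but it is not needed for a gap of this size.
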